##### Functional disability

The Blepharospasm Disability Index (BSDI)© [15, 16] is a patient self-report measure that asks about six daily activities: reading, driving a vehicle, watching TV, shopping, walking and doing everyday activities. The measure is also recommended for use in hemifacial spasm [14]. Each activity is rated on a scale from 0 = no impairment to 4 = no longer possible due to my illness, and a ‘not applicable’ option is also available. The scoring system is a mean item score, calculated by dividing the sum score by the number of applicable items. Sum scores, therefore, range from 0 to 4 with higher scores indicating greater disability. A 0.7-point improvement in the BSDI© mean item score is considered a clinically relevant improvement [13]. However, this criteria is only relevant for patients whose baseline scores are >0.7 [13]. The measure possesses good convergent validity with the JRS, good internal consistency (Cronbach’s alpha = 0.88) and adequate test-retest reliability [13].

##### Patient satisfaction

Patient satisfaction will be measured using the eight-item Client Satisfaction Questionnaire (CSQ; [17]). Responses to each of these eight items range on a Likert scale from 1 to 4, each item has different weighted responses and patients will be instructed to answer in response to the care they receive in the nurse-led botulinum toxin clinic. Items include ‘How would you rate the overall quality of the service your received?’. Scale scores are a sum of the eight items and range from 8 to 32, with higher scores indicating greater satisfaction. The scale has good internal reliability, with a Cronbach’s alpha of 0.93 and good construct validity [18].

#### Secondary outcome measures

##### Quality of life

Quality of life will be measured using the Craniocervical Dystonia Questionnaire (CDQ-24; [19]), which was developed and validated in patients with blepharospasm and has also been used with success in patients with hemifacial spasm [20]. This 24-item measure assesses quality of life across five domains: stigma, emotional well-being, pain, activities of daily living and social/family life. Each item consists of five statements representing increasing severity of impairment and is scored from 0 to 4. In order to obtain comparable scores for the individual subscales, raw sub-scores (= sum of the individual item score) are linearly transformed to a 0–100 scale, where a score of 0 indicates the best and a score of 100 the worst possible quality of life. The measure has been found to possess good internal consistency with Cronbach’s alphas ranging from 0.77 to 0.89, good construct validity when compared who the Short Form 36 (SF-36), good discriminant validity and test-retest reliability [20].

##### Mood

The Hospital Anxiety and Depression Scale (HADS; [21]) will be used to assess mood. The HADS is a 14-item self-screening questionnaire for depression and anxiety in patients with physical health problems and the two 7-item subscales measure how the respondent has been feeling in the past week. The scale scores range from 0 to 21, with higher scores indicating greater levels of anxious or depressed mood. A score of 0–7 on either subscale is regarded as being in the ‘normal’ range, a score of 8–10 is suggestive of the presence of moderate levels of anxiety or depression, and a score of 11 or above indicates ‘caseness’, a high likelihood that a person would be diagnosed with clinical anxiety or clinical depression. A systematic review of the HADS has confirmed the factor structure and found the cut-off points to be valid against clinical interviews [22]. This tool has demonstrated high internal consistency (*r* = 0.76 to 0.41 for anxiety scale items and *r* = 0.60 to 0.30 for depression scale items) and good reliability [23].

##### Illness beliefs

Illness perceptions are cognitive representations or beliefs that a patient has about their illness. These concepts will be measured using the revised Illness Perceptions Questionnaire Revised (IPQ-R; [24]) that assesses each of the components of illness representations (Table 1).

**Table 1 Tab1:** Definitions of the Illness Perceptions Questionnaire Revised (IPQ-R) subscales

Subscale	A belief…..
Cause	…about the cause of my illness
Identity	…about the number of symptoms attributable to their condition
Time (acute/chronic)	…about the duration of the condition
Consequences	…that their condition will have serious consequences
Personal control	…in one’s ability to personally influence the outcome of their condition
Treatment control	…that medical treatments will be effective in controlling their condition
Illness coherence	…that condition ‘makes sense’
Timeline cyclical	…that the condition will come and go in cycles
Emotional representations	…that the condition is emotionally distressing

Total scores on the illness identity subscale range from 0 to 14 and higher scores represent strong beliefs about the number of symptoms attributed to their condition. In order to increase the face validity of this subscale four blepharospasm and hemifacial spasm symptoms were added to the identity scale: (1) frequent blinking, (2) irritation of the eye, (3) uncontrollable eye closure and, and (4) muscle twitching around the face and/or eye; bringing the maximum score up to 18. Total scores range from 6 to 30 for the consequences, timeline acute/chronic, emotional representation and personal control subscales and 5–25 for treatment control and illness coherence and 5–20 for timeline cyclical. High scores represent strongly held beliefs about their condition. The subscales have been found to possess good internal consistency [25]. Cause is assessed in 18 items which are analysed in three groupings, causes relating to psychological attributions, risk factors and immunity. Each of these subscales possesses good internal consistency ranging from 0.67 for immunity to 0.86 for the psychological attribution subscale [25]. Participants are also asked to rank the three most important factors that they believe caused their illness.

##### Treatment beliefs

Beliefs about botulinum toxin will be measured using the Treatment Representations Inventory (TRI; [21]); a 27-item measure, consisting of four scales measure on a 5-point Likert agreement scale. Scales include treatment-value, treatment-concerns, decision-satisfaction and cure. Scales demonstrate good internal consistency (Cronbach’s alpha: 0.78, 0.77, 0.80 and 0.75 respectively).

##### Confidence

Confidence in the service will be assessed using a 10-cm visual analogue scale (VAS), as in other evaluations of patient-initiated services [24, 26, 27]. Participants will be asked ‘How confident are you that if you required treatment this system of care would be able to support you?’, ranging from ‘not at all confident’ to ‘completely confident’. Individual side effects will also be recorded at each clinic visit by the treating healthcare professional along with a subjective assessment of the duration of beneficial effect of their last treatment, in weeks.

##### Acceptability

Acceptability of the new patient-initiated service and standard care will be measured using the seven-item Acceptability Questionnaire [28]. Responses are on a Likert scale from 1 to 5 and response labels vary depending on the item, for example, ‘How fair do you feel this system has been?’ has the response options ‘not at all fair’ (1) to ‘very fair’ (5). The questionnaire will be validated using established methods once all data has been collected.

##### Health-care usage

Use of health and social care services will be estimated using a brief version of the Client Service Receipt Inventory (CSRI; [29]) completed by a combination of self-report and electronic patient records (EPR). The CSRI has been validated and widely employed in previous studies, particularly in the mental health setting [29] and has been found to be a suitable tool for use with patients experiencing psychological distress [30].

##### Cost-effectiveness

The impact of the service on direct and indirect costs will be estimated at the end of the trial period using this brief CSRI [29]. This data will be collected by the research nurse at the 9- month follow-up visit, who will ask participants to report which services they have accessed in the past 9 months. This information will be cross-referenced with each patient’s hospital notes to minimise recall bias. The accurate collection of resource-use data is commonly a challenge in economic evaluation and the method of comparing patient self-report to healthcare records has been used in recent research [31]. Unit costs of healthcare resources will be derived from the NHS trust where possible. For sensitivity analysis, and/or where there is an absence of costs available locally, national unit costs that are judged representative of local costs will be obtained from national sources, such as NHS Commissioning or NHS England. Costs associated with the different resources and services will be reported as part of this economic evaluation. To calculate the costs, we will look at: (1) resource use in primary care, including an examination of total botulinum toxin used, visits to the GP, and other services, (2) resource use in secondary care including attendance at accident and emergency clinics (A&E), (3) resource use from specialty services, (4) intervention costs and costs of treatment as usual for comparison, (5) resources associated with any admissions will be recorded and totalled with all the previously identified resources, to calculate a total cost to the health service overall, (6) resource use in social care including social worker and community psychiatric nurse, and (7) out-of-pocket costs to the individual such as visual aids and travel to appointments. Out-of-pocket costs, including the cost of visual aids, to the individual will also be recorded at baseline. A fuller description of the methods used to conduct the cost-effectiveness analysis is described in the statistical methods section.

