### Procedures

Invitation letters will be sent to eligible patients 2 weeks prior to their outpatient appointment in the nurse-led botulinum toxin clinic by the trial co-ordinator. On the day of the appointment the patient will be approached by the research fellow to participate in the study. Those who agree will be consented into the trial by the research fellow. Qualitative data will be collected on reasons for refusal. Baseline assessment questionnaires will be given to participants consenting to take part in the study with a freepost envelope for return, all subsequent follow-up self-report questionnaires will be sent to the participants’ home also with a freepost envelope for return. Participants who do not return questionnaires within 2 weeks will be contacted by telephone. If participants do not respond to one follow-up telephone call and one letter, and there is no evidence that the patient has moved, it will be considered that they no longer wish to take part in the trial and they will not be sent further questionnaires. They will continue in the trial on the basis that clinical and cost-effectiveness data can still be collected and an intention-to-treat analysis (ITT) will be performed. Participants in the intervention trial arm who no longer wish to take part in the trial but are happy to continue to complete questionnaires will also be included in the ITT analysis.

Disease severity and function will be assessed at baseline and then at each clinic visit by the treating healthcare professionals and again 2 weeks after treatment via telephone by the research fellow.

Participants in the intervention group who have agreed to be contacted about an interview to assess acceptability of the new service will be followed up with a telephone call by a research assistant to arrange a time and place for the interview. Participants will be interviewed after their 9-month participation in the trial has ended.

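### In-trial self-reported resource use is taken once, at the 9-month visit with a 9-month recall, and hospital records are unlikely to check or replace its non-hospital items

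*Protocol article*

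**What the plan says.** The Cost-effectiveness section of the protocol article sets the schedule for the brief CSRI: "This data will be collected by the research nurse at the 9- month follow-up visit, who will ask participants to report which services they have" used, with a look-back of 9 months ("report which services they have accessed in the past 9 months"). It names one safeguard: "This information will be cross-referenced with each patient’s hospital notes to minimise recall bias". The Health-care usage section adds electronic patient records as a source alongside self-report.

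The same Cost-effectiveness section lists what is to be costed. The list includes GP visits (item 1), social worker and community psychiatric nurse contacts (item 6), and visual aids and travel (item 7). It also provides for one earlier record: "Out-of-pocket costs, including the cost of visual aids, to the individual will also be recorded at baseline".

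The Procedures section says of the other measures that "all subsequent follow-up self-report questionnaires will be sent to the participants’ home also with a freepost envelope for return". For people who stop answering that post it says: "They will continue in the trial on the basis that clinical and cost-effectiveness data can still be collected".

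Under Difference in mean costs, all these items are added into one total per patient. The arms are compared on that total, and cost-effectiveness ratios are bootstrapped from the cost and effectiveness data.

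**The concern.** Two things depend on a single interview. The first is accuracy: 9 months is a long time over which to remember GP appointments, social-care contacts and small personal expenses, and the stated check draws on records that would not normally contain them. The second is completeness: with nothing taken at 3 months or on leaving, a participant who drops out at month 4, say, loses the self-reported use of months 0 to 4 as well as the later months.

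What is at stake is the between-arm cost difference. For someone who misses the visit, the total is either missing or made up of hospital items only, and so too low. Cost-effectiveness is a secondary aim, but the article's Discussion makes it part of the case for changing services.

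**Working it through.** The article states no figure on this point, so the check is mainly a reading of its sections side by side.

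**1. Is there another in-trial collection?** The Outcomes section says in general that self-report measures are repeated at 3 and 9 months. The Cost-effectiveness section is specific to the CSRI: collected by the nurse, at 9 months, covering the whole 9 months. A 9-month look-back would not be needed if a 3-month form were planned, and none is described. The baseline record of out-of-pocket costs exists, but it cannot cover spending during the trial.

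**2. Which items have a second source?**

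| Item | In-trial source besides the 9-month interview |
|---|---|
| Toxin and dose | Collected across the trial (Outcomes) |
| Clinic visits | Intervals recorded in both arms (Frequency of outpatient visits) |
| Admissions and other care at the hospital | Hospital notes, electronic records |
| Travel to the clinic | Not recorded, but could be estimated from postcode (Outcomes) and visit records |
| GP visits | None likely in hospital records |
| Social care | None likely in hospital records |
| Visual aids and other personal expenses | None likely in hospital records |

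For the last three rows the interview is the only in-trial source. This is true of full completers too, so the recall problem does not depend on dropout.

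**3. How would non-attendance enter the cost difference?** Suppose hospital-only totals were used for non-attenders; the article does not say that they would be. Let p₁ and p₀ be the proportions not attending in the intervention and control arms, and N₁ and N₀ the mean non-hospital costs, with non-attendance unrelated to cost. Then

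observed difference = true difference − (p₁N₁ − p₀N₀).

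- Equal non-attendance (p₁ = p₀ = p): the error is p(N₁ − N₀), so the non-hospital part of the difference shrinks by the factor (1 − p).
- Equal non-hospital cost (N₁ = N₀ = N): the error is N(p₁ − p₀), which vanishes only if non-attendance is equal in the two arms.

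The article gives none of p₁, p₀, N₁ or N₀, so no value can be put on the error.

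**4. Scale.** The planned sample is 266 (Abstract). Assuming 10% to 30% non-attendance: 0.10 × 266 = 26.6 and 0.30 × 266 = 79.8, or about 27 to 80 participants without self-reported use.

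**5. What would a 3-month form recover?** For those who return it, the longest recall falls from 9 months to 9 − 3 = 6. A person leaving at month 4 would keep 3 of 4 months from that form, and all 4 if a form were also completed on leaving.

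**The case against.** A reader might infer that the article contradicts itself, since Procedures says that cost data can still be obtained from people who stop responding. The text does not support this. That sentence applies to a defined group: "If participants do not respond to one follow-up telephone call and one letter, and there is no evidence that the patient has moved". These people stay in the trial. The CSRI is not described as part of the post they have stopped answering; the nurse takes it at a visit. Every participant is given a 9-month appointment (Intervention) and is booked back into the clinic automatically at the end of the trial period (Patient safety). Nothing is promised about people who move, withdraw fully or miss the visit. The sections are compatible. For postal non-responders, the assurance on self-reported costs simply holds only if they attend.

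Three other objections have weight.

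- The major hospital items do not depend on the interview, and travel to the clinic could be estimated. This stands, and it narrows the concern to non-hospital items.
- A postal CSRI will not reach people who ignore post. This also stands, and is a reason to keep the nurse's collection at 9 months and add to it. The 3-month form helps those who are still responding then and later leave or fail to attend.
- Handling of missing cost data may be set out in a full protocol or analysis plan that is not shown. That is fair, and its absence here is not criticised. The collection schedule itself is stated in the article, however, and no later analysis can recover use that was never asked about.

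**Conclusion.** The point holds as a design weakness in a secondary outcome, not as an inconsistency. Self-reported use of non-hospital services during the trial rests on one 9-month recall that the named records are unlikely to verify, and it is lost altogether for anyone who does not attend at 9 months. That hospital records lack these items is a judgement about what such records usually contain; the article does not say so.

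The size of any bias is unknown. It is tempting to apply the 79% completion rate from the Sample size section and conclude that 0.21 × 266 = 55.9, about 56 participants, would lack these data, and then to multiply by an assumed non-hospital share of cost to obtain a percentage understatement. The documents do not support either step: the 79% is a completion rate taken from another trial for sample sizing, not an attendance rate for a 9-month treatment appointment, and no cost share is given. Differential loss between arms is possible, but nothing in the article shows it.

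This is a cheap improvement.

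**What to change.** - Add the brief CSRI to the existing 3-month questionnaire pack, covering months 0 to 3.
- When a participant in either arm withdraws, and agrees, complete the CSRI by telephone or post for the time since the last report.
- Keep the nurse's CSRI at 9 months but limit it to the time since the last report, or the full 9 months where there is none.
- State in the Cost-effectiveness section that hospital notes verify hospital items only.

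Leavers who complete these forms then contribute observed costs up to their last report, and only the remaining months have to be treated as missing. The cost is one or two more pages at 3 months, a short form at withdrawal, and a mix of postal and nurse collection, so the mode used should be recorded with each form. Clinical management does not change.

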##### Frequency of outpatient visits

The length of time between visits to the nurse-led clinic will be recorded (in days) for participants in both arms of the trial. In the patient-initiated treatment group the reasons for initiating a consultation will be recorded at the time of initiating the appointment.

##### Adverse effects

The frequency of adverse events including ptosis, double or blurred vision, tearing, hematoma and foreign body sensation will also be recorded at each clinic visit as either present or absent. Patients will also be followed up 2 weeks after each visit in which they receive botulinum toxin treatment to assess any adverse events.

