### Intervention

Participants randomised to the intervention group will initiate their own treatment during the trial period (9 months). They will be given information about when and how to initiate an appointment in the nurse-led botulinum toxin clinic, in a leaflet sent to them by a trial co-ordinator after randomisation. Participants will be asked to contact the service when they feel their symptoms are returning at a sufficient level for them to seek medical help. Contact details for the service will also be provided along with information on how quickly an appointment will be made, with whom, and the procedure in the case of an emergency. Receipt of the leaflet will be followed by a telephone call from one of the research team to answer any questions participants may have. When participants in the intervention group contact the service to book an appointment they will be triaged by the trial co-ordinator. All patients with an activity score of 1 or above on the Jankovic Rating Scale (JRS; [12]) will be booked in to the next available slot within the twice-weekly nurse-led outpatient clinics, estimated within a 2-week period from the initial call. There will be no upper limit for the number of times participants in the intervention group can initiate an appointment. However, participants will be advised to wait 2 weeks after botulinum toxin treatment as this is the time it takes to reach effectiveness. It is, therefore, estimated that participants would not return to the clinic within 3 to 4 weeks of their previous appointment. All participants will be given an appointment at 9 months to meet safety criteria for any patients who do not seek an appointment during their participation in the trial.

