#### Control group

Participants in the control group will receive usual care. This consists of scheduled appointments in the nurse-led outpatient botulinum toxin clinic, usually every 3 months.

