### Outcomes

Participants will be in the trial for 9 months. An initial baseline assessment will be taken by a research fellow prior to randomisation; this will include the full range of measures. Self-report measures will be taken again at 3- and 9-month follow-ups.

At baseline, demographic information will be collected using self-report measures including: date of birth, gender, marital status, ethnicity, postcode, number of years of schooling, highest completed level of education and further education. Data will also be collected from the patients’ medical notes on diagnosis, year of diagnosis, duration of botulinum toxin treatment, number of previous cycles, frequency of previous cycles, last dose, and co-morbidities. The total number of botulinum toxin injections and dosage received by the patient across the trial period will be collected.

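### Adverse events are looked for only at clinic visits and two weeks after injections, so the number of checks per patient depends on the attendance that randomisation changes

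*Protocol article*

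**What the plan says.** All references are to the protocol article.

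- **Adverse effects** (secondary outcome measures): the outcome is "The frequency of adverse events including ptosis, double or blurred vision, tearing, hematoma and foreign body sensation", and it "will also be recorded at each clinic visit as either present or absent". A second occasion follows: "Patients will also be followed up 2 weeks after each visit in which they receive botulinum toxin treatment to assess any adverse events". The present/absent format is given for visits; no format is given for the two-week contact.
- **Confidence**: "Individual side effects will also be recorded at each clinic visit by the treating healthcare professional". The Blinding section says that these professionals are not masked.
- **Control group**: "This consists of scheduled appointments in the nurse-led outpatient botulinum toxin clinic, usually every 3 months".
- **Intervention**: "There will be no upper limit for the number of times participants in the intervention group can initiate an appointment". The same section gives an expected lower bound on spacing: "It is, therefore, estimated that participants would not return to the clinic within 3 to 4 weeks of their previous appointment". The only appointment that every intervention patient is sure to be given is the one at 9 months.
- **Outcomes**: "Self-report measures will be taken again at 3- and 9-month follow-ups". No adverse-event item is named among these measures. The section also says that the number of injections and the dosage over the trial are collected.

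**The concern.** Every described occasion for recording an adverse event is created by an attendance or an injection, and the trial randomises who decides when those happen. A patient who comes often is asked often; a patient who stays away is hardly asked. If the arms are compared on patients with an event, or on events per patient, the result reflects both how often events occur and how often anyone looked. Frequent attenders could appear to have more harm, and rare attenders less, with no difference in underlying risk.

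A counting rule set later in an analysis plan can deal with part of this. It cannot recover assessments that never took place.

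**Working it through.** The article states no number of assessments and no adverse-event rate, so there is no figure of its own to reproduce. The looks can be counted from the stated schedule.

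**Inputs from the article.** Trial length 9 months, about 39 weeks (Outcomes); control visits about every 13 weeks (Control group); shortest expected intervention interval 3 to 4 weeks, and a 9-month appointment for all (Intervention); one contact two weeks after each treated visit (Adverse effects).

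**Assumptions.** Treatment is given at the enrolment visit (week 0) and at each later visit before week 39. The week-0 record and any contact after week 39 are not counted.

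| Pattern | Visits (week) | Two-week contacts (week) | Looks | Longest gap |
|---|---|---|---|---|
| Control, 13-weekly | 13, 26, 39 | 2, 15, 28 | 3 + 3 = 6 | 11 weeks |
| Intervention, 4-weekly | 4, 8, ..., 36, 39 | 2, 6, ..., 38 | 10 + 10 = 20 | 2 weeks |
| Intervention, 8-weekly | 8, 16, 24, 32, 39 | 2, 10, 18, 26, 34 | 5 + 5 = 10 | 6 weeks |
| Intervention, 16-weekly | 16, 32, 39 | 2, 18, 34 | 3 + 3 = 6 | 14 weeks |
| Intervention, never initiates | 39 | 2 | 1 + 1 = 2 | 37 weeks |

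**Effect on a per-patient frequency (illustration).** Suppose that each look independently yields a positive record with probability p, the same in everyone. The chance of at least one record in n looks is 1 − (1 − p)^n.

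| Assumed p | n = 2 (never initiates) | n = 6 (control) | n = 20 (4-weekly) |
|---|---|---|---|
| 2% | 4% | 11% | 33% |
| 5% | 10% | 26% | 64% |
| 10% | 19% | 47% | 88% |

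The percentages depend on p; their order does not.

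**Arm level.** These are patient types, not arms. As an extreme mix, let a share s of the intervention arm return 4-weekly and the rest never initiate. The mean number of looks equals the control figure when 20s + 2(1 − s) = 6, so s = 4/18 = 2/9. At p = 5% the share of the arm with at least one record is then 2/9 × 64.2% + 7/9 × 9.75% = 21.8%, against 26.5% in control. With equal average looks, the distortion in this example is therefore about 5 percentage points.

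**Per injection.** Injections before week 39 number 3 (control), 10 (4-weekly) and 1 (never initiates), and two-week contacts number 3, 10 and 1. That is one two-week look per injection in every pattern.

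**Meaning of a visit record.** The article does not say whether a record covers the present moment or the time since the last visit. On the first reading the number of looks is unequal; on the second, the recall windows are unequal (about 4, 13 or 39 weeks). Neither reading makes the visit data directly comparable.

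**The case against.** The case on the other side is substantial, and much of it stands.

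- **Safety is not a stated aim.** A reader might infer that the trial sets out to show that patient-led timing is safe. The aims at the end of the Background section do not say so, adverse events are not among the outcomes listed for the multilevel models, and the Discussion anticipates no safety concerns. The outcome is secondary.
- **Looks per injection are balanced.** The two-week contact follows every treated visit in both arms, and most of the listed events are effects of injection. More events arising from more injections are a real consequence of the care model, and the long gap falls in patients who have had no new injection.
- **Double counting is not established.** A reader might infer that one lasting event is counted twice in patients who return soon. An event lasting 4 weeks from injection would be present at 2 looks with a 4-week interval and at 1 with a 13-week interval. It counts twice only if positive contacts are summed. The article states no counting unit, and an analysis plan may set one.
- **Non-attenders are not invisible.** A reader might infer that harm from late treatment goes unrecorded until month 9. The postal self-report measures at 3 and 9 months, including the disability index, do not depend on attendance. The service-use inventory covers A&E visits, GP visits and admissions over the 9 months, checked against hospital notes. An external monitor also looks for unrecorded events.
- **The percentages are illustrative.** A constant, independent chance per look ignores time since injection, and arm averages may be close.

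What remains is narrower. None of these sources is described as an adverse-event check at the same times in both arms before month 9, and the monitoring and safety sections describe no further patient contact for that purpose.

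**Conclusion.** The point holds as a limitation of how a secondary outcome is collected. Ascertainment follows attendance, and attendance follows the randomised arm. Within 39 weeks the number of looks runs from about 2 to about 20 in the intervention arm (26 at the 3-week end of the expected spacing), against about 6 in control. Any per-patient adverse-event frequency would carry that difference.

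The counts rest on treatment at enrolment and at each later visit, and on evenly spaced visits. The size of any bias between arms cannot be derived from the article, because it depends on how often intervention patients attend and on the chance of a report at each look. It could be small if average attendance is similar. The two-week data, expressed per injection, are sound for comparison. This is a cheap improvement to make, not a threat to the primary analysis.

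**What to change.** 1. Add a short adverse-event checklist, with approximate onset and end of each event, to the 3- and 9-month questionnaires that both arms already receive. Report patients with at least one event over these equal windows beside the clinic-recorded data. This gives both arms two shared look times and shortens the longest gap for a patient who never initiates from about 37 weeks to about 26 (39 − 13).
2. Report the visit and two-week data per injection, using the injection totals already collected, and count each episode once. State whether a visit record means present now or since the last visit.

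The cost is part of a page on an existing form and a sentence in the analysis section. The downsides are recall over 3 to 6 months and dependence on questionnaire return, for which the Sample size section assumes 79% completion. The checklist should therefore supplement the two-week contacts and not replace them. No treatment schedule changes.
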